### Study components

Data collection will consist of three main components:
*Household surveys of malnutrition risk factors*. To evaluate the impact of the intervention on known malnutrition risk factors two detailed household surveys will be implemented, the baseline survey will be undertaken before the intervention begins and the endline one 3–4 months after the start of the intervention.Based on our working assumption that insecurity in the field will constrain the possibility of following-up the baseline sample, the surveys will select independent samples of households from the study clusters at the two periods. If security conditions are worse than anticipated and do not allow sampling within a sufficient number of clusters, then we will collect data from a single control and intervention cluster and the data will be analysed as a before and after comparative cross-sectional study. Furthermore, if security conditions do not allow us to undertake repeated surveys in the same clusters, then we will undertake a single survey at the end of the intervention, and the data will be analysed as a cross-sectional study. However, if field conditions are better than anticipated, we will follow-up the baseline sample and the data will be analysed as a longitudinal cohort.The surveys will collect data at the household level and from all the children aged <5 years and their mothers/carers living in the selected households. The data collected in these surveys will comprise data on household demographics, household expenditure and income, assets, food security, diet diversity, coping strategies, morbidity, WASH, access to health care, and infant and young child feeding practices. The surveys will also collect anthropometric data from children to describe their nutritional status. However, this anthropometric data will not be used to assess the impact of the intervention due to sample size limitations (see below).
*A community surveillance system* will be set up to collect anthropometric data that will be used to evaluate whether the intervention reduces the risk of developing acute malnutrition. In this surveillance system, community health workers (CHW) will collect monthly mid-upper arm circumference (MUAC) measurements to detect the incidence of acute malnutrition in an exhaustive sample of children aged 6–59 months from both intervention and control clusters. Those identified as malnourished will be referred to nutrition centres for treatment.

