### Sample size calculation

Sample size calculations were performed using Stata (StataCorp. 2015. Release 14. College Station, TX: StataCorp LP). For assessing the change in malnutrition risk factors using survey methods, the sample size was estimated to be able to detect a difference of 0.6 units in the mean individual dietary diversity score (IDDS). A positive change of about 2 units in the household diet diversity score was observed in response to a social CTP in Malawi [15]; but other studies had lower changes [16, 17]. There is little data on IDDS change following cash transfers so we decided to power the study to detect a conservative change, assuming a baseline IDDS of 3.0 with a SD of 1.5, with power of 80%, an alpha risk at 0.05, and an intra-cluster correlation coefficient of 0.01. The resulting required sample size was 120 children per arm. Based on previous nutrition survey data we assumed an average of 1.2 children, aged 6–59 month per household, which implies that 200 households will need to be sampled during each data collection period. Based on previous survey experience, we added 20% to allow for non-response leading to a required total sample of 240 households.

To assess malnutrition incidence using the community surveillance system and detect a hazard ratio of 0.5, we assumed, based on operational guidance for caseload estimations, that the proportion of the population under surveillance that would develop GAM during 6 months was 7%, and there would be 20% loss to follow up. Power was set at 80% and the alpha risk at 0.05. This resulted in a total sample size of 1167 children, which equated to a rounded sample of 600 participants per arm. Because data will be obtained from an exhaustive sample of children in both control and intervention clusters, we expect to have a greater sample.

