### Data analyses

Data analysis will be undertaken using Stata. Prevalence estimates at baseline and endline, will be computed using the *svy* commands which allows for the clustering of values. We will test for endline minus baseline difference-in-differences between the study arms using the data collected in the malnutrition risk factor surveys. Analysis of the incidence of acute malnutrition in the trial arms will be performed using Cox Proportional Hazards analysis. All results will be reported according to STROBE recommendations for observational studies [21].

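### The 1167 children for the incidence outcome require 7% to be the event risk averaged over both arms at a hazard ratio of 0.5. If 7% is the risk without the intervention, as its source suggests, 6-month power is about 68% rather than 80%.

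*Protocol article*

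**What the plan says.** The section Sample size calculation sets the incidence component up to "detect a hazard ratio of 0.5", with power 80% and alpha 0.05. Its event-rate input is introduced with the words "we assumed, based on operational guidance for caseload estimations", and is that "the proportion of the population under surveillance that would develop GAM during 6 months was 7"%. It adds that "there would be 20% loss to follow up". The result follows: "This resulted in a total sample size of 1167 children, which equated to a rounded sample of 600 participants per arm". The section then says that the real sample is expected to be larger because sampling is exhaustive, but gives no number.

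The section Study components describes the surveillance sample as "an exhaustive sample of children aged 6–59 months from both intervention and control clusters". The analysis is fixed in Data analyses: "Analysis of the incidence of acute malnutrition in the trial arms will be performed using Cox Proportional Hazards analysis". Under Outcome measures, incidence of acute malnutrition is the first of two primary outcomes.

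No separate control-arm and intervention-arm risks are given. The article does not say whether the 7% already allows for the assumed halving of the hazard in one arm.

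**The concern.** The power of a Cox comparison depends on the number of events. To turn required events into children, one divides by the event probability averaged over both arms under the alternative hypothesis. If the available figure is a background risk, it belongs to the control arm, and the average must be reduced because the intervention arm is assumed to have half the hazard. Entering the background risk directly as the average overstates the expected events and so the power.

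The stated source, "based on operational guidance for caseload estimations", points to a background risk. Nothing in the article suggests that such guidance would already average in a halving produced by this cash, kit and water package in half of the children. What is at stake is the stated 80% for a primary outcome. If the true figure is nearer 68%, the chance of missing a real halving of the hazard is about 32% rather than 20%, and a null result could be read as stronger evidence of no effect than it is.

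**Working it through.** **Inputs** (all from Sample size calculation): hazard ratio 0.5; 7% over 6 months; 20% loss; power 80%; alpha 0.05; equal arms. Sidedness is not stated; two-sided reproduces the printed total. No clustering is included anywhere below.

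**1. Reproducing the printed total.**
- Events (Schoenfeld, 1:1): 4 × (1.960 + 0.842)² / (ln 0.5)² = 4 × 7.849 / 0.48045 = 65.35.
- Children: 65.35 / (0.07 × 0.80) = 1166.9, that is 1167.

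So 7% was used as the two-arm average. Using 7% as the control risk gives quite different totals: about 1547 (Schoenfeld), 1672 (Freedman) and 1593 to 1660 (two proportions). None is near 1167.

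**2. What a two-arm average of 7% implies.** Let c be the control risk and s = √(1 − c). With proportional hazards and a ratio of 0.5, the intervention risk is 1 − s.
- (1 − s² + 1 − s) / 2 = 0.07, so s² + s − 1.86 = 0 and s = 0.9526.
- Control risk: 1 − s² = 9.3%. Intervention risk: 1 − s = 4.7%.

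Neither figure appears in the article.

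**3. If 7% is the risk without the intervention.**
- Intervention risk: 1 − 0.93^0.5 = 3.56%.
- Two-arm average: (7.00 + 3.56) / 2 = 5.28%.
- Power = Φ(½ × √events × ln 2 − 1.96).

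| Children | Events (N × 0.80 × 0.0528) | Power over 6 months |
|---|---|---|
| 1167 | 49.3 | 68.2% |
| 1200 (600 per arm) | 50.7 | 69.4% |

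- Size for 80% power: 65.35 / (0.05282 × 0.80) = 1546.5, that is about 1547 children. This is 1547 / 1167 = 1.33 times the printed total.

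**4. Sensitivity on this reading.**
- Lost children contribute half of their follow-up (effective retention 90%): power 73.3% at 1167 and 74.5% at 1200.
- A two-proportion test at 1167 with 20% loss: 65% to 67%.

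**5. Longer follow-up on this reading,** with constant hazards and 1167 children:
- 8 months: risks 1 − 0.93^(8/6) = 9.2% and 1 − 0.93^(4/6) = 4.7%; average 6.97%; with 20% loss, 65.1 events and 79.8% power.
- 12 months: risks 13.5% and 7.0%; average 10.26%; with 20% loss, 95.7 events and 92.4% power. With 36% loss (1 − 0.80²), 76.6 events and 85.8% power.

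**The case against.** Three points can fairly be made for the article.

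First, the text is consistent if read literally. Surveillance covers both arms, so a proportion of the population under surveillance is a two-arm proportion. That is the quantity the formula needs, and 1167 and 80% then follow exactly. This stands. A reader might conclude that the calculation contains an arithmetic error, or that 1167 children give 68% power without qualification. The article does not support either conclusion: the stated inputs give the stated output, and the 68% depends on an inference about the 7%. What the literal reading does not supply is any basis for a 9.3% control risk, or a reason why general caseload guidance would describe a mixture of treated and untreated camps.

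Second, 1167 is a minimum. Sampling is exhaustive in 20 camps, and about 1547 children would be roughly 77 per camp. This also stands. A reader might infer that the trial is underpowered, but camp sizes are not given, so no shortfall in the children actually followed is shown. Equally, an expectation of more children without a number does not show that the higher figure is reached.

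Third, the section Data collection plans surveillance for about 1 year. On the control-risk reading, 8 months of follow-up would already bring power back to about 80%. This stands in part. It needs the halving to persist beyond the 5 months of transfers, Table 1 displays only February to August, and the Discussion reports that the transfers started in May rather than March. The sample size itself is framed over 6 months.

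**Conclusion.** The point holds as a problem with one input. The printed 1167 treats 7% as the two-arm average under a hazard ratio of 0.5, while the attribution of that 7% makes it most plausibly the risk without the intervention. Over 6 months the article supports a range: 80% power at 1167 if 7% is truly the average, and about 68% (69% at 600 per arm) if it is the control-arm risk. The lower end rests on a two-sided 0.05 test, proportional hazards, 20% loss applied as in the article, and no design effect. The absence of a design effect is a separate matter; this point would remain if children had been allocated individually.

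The practical weight is moderate. It concerns a figure stated for a primary outcome, but a larger exhaustive sample or follow-up beyond 6 months may make up the difference.

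**What to change.** In Sample size calculation, treat 7% as the control-arm 6-month risk, derive the two-arm average under a hazard ratio of 0.5 (5.3%), and restate one of two figures: the requirement, about 1547 children in total before any design effect, or the power at 600 per arm, about 69% before any design effect. If 7% was meant as the two-arm average, say so, state the implied control-arm risk of about 9.3%, and give its basis.

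In either case, add the power for the number of children actually under surveillance and for the follow-up period that the Cox analysis will use.

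The cost is one recalculation and a few reworded sentences. No extra enrolment is needed, because surveillance is already exhaustive in the study camps. The only downside is a less favourable stated figure.

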### Study design

The study design is a non-randomised cluster controlled trial. Concern will implement a routine needs assessment exercise to identify vulnerable beneficiaries and on that basis select the camps that will receive the intervention. All households in the selected camps will be registered for the intervention. A non-randomised design was chosen as the best available approach in this setting because the intervention will be allocated based on vulnerability criteria.

The cluster unit in the trial will be an IDP camp and the intervention arm will include 10 IDP camps selected to receive the intervention. The reason that only 10 camps can be selected to receive the intervention is the limit in the donor funding that is available to provide services in this area. The control arm will include another 10 IDP camps, located adjacent to the intervention camps that will not receive the intervention. Routine programme data suggests small differences in vulnerability between camps. Households in both arms will benefit from the services provided by Concern, such as care from OTP and MCHN centres.

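### The 1167-child size for the primary incidence outcome contains no allowance for camp clustering, so the stated 80% power does not describe the cluster design at 600 children per arm

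*Protocol article*

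**What the plan says.** All references are to the protocol article.

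- **Outcome measures** names incidence of acute malnutrition, by arm circumference or oedema, as the first primary outcome. Mean individual dietary diversity score is the second.
- **Study design** makes the camp the unit of allocation: "The cluster unit in the trial will be an IDP camp and the intervention arm will include 10 IDP camps". The control arm has another 10. The section gives the limit on donor funding as the reason for only 10 intervention camps.
- **Sample size calculation**, first paragraph, sizes the dietary diversity survey with "an intra-cluster correlation coefficient of 0.01".
- **Sample size calculation**, second paragraph, sizes the incidence outcome. Its inputs are "To assess malnutrition incidence using the community surveillance system and detect a hazard ratio of 0.5", a 7% six-month risk of acute malnutrition, "there would be 20% loss to follow up", and "Power was set at 80% and the alpha risk at 0.05". The result is "This resulted in a total sample size of 1167 children, which equated to a rounded sample of 600 participants per arm". The list contains no ICC, design effect or number of camps. The paragraph ends by saying that a larger sample is expected because all children in the study camps will be measured. It gives no number.

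**The concern.** When whole camps are allocated, children in the same camp carry partly overlapping information about the intervention effect. A size derived for independent children then overstates power. The section recognises this for the survey outcome and not for incidence, where it matters more: 600 children in 10 camps is 60 per camp, against 120/10 = 12 per camp in the survey, five times as many.

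Incidence is the outcome that carries the main hypothesis. If the 80% is taken at face value, a hazard ratio whose interval includes 1 may be read as evidence against a halving of risk, when the design had a materially smaller chance of detecting one.

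**Working it through.** **Inputs.** Hazard ratio 0.5, six-month risk 7%, loss 20%, power 80% and alpha 0.05 (Sample size calculation); 10 camps per arm (Study design). Two-sided alpha is not stated but is the choice that reproduces the printed figure. The ICC of 0.01 comes from the survey calculation and is borrowed here. ICCs of 0.005 and 0.02 are assumptions, to show sensitivity.

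**1. Reproduce the plan's figure.**
- Events (Schoenfeld, 1:1): 4 × (1.960 + 0.842)² / (ln 0.5)² = 65.35.
- Children: 65.35 / 0.07 = 933.5; 933.5 / 0.80 = 1166.9, that is 1167.

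The match is exact with a design effect of 1.

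**2. Power at 600 per arm with clustering.** Expected events: 1200 × 0.80 × 0.07 = 67.2. Design effect: DE = 1 + (m − 1) × ICC, with m children per camp. Power = Φ(0.693 × √(67.2 / DE / 4) − 1.96). Loss has already been taken out of the events, so the count of m needs care. Both counts are shown.

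| ICC | DE, m = 60 enrolled | Power | DE, m = 48 retained | Power |
|---|---|---|---|---|
| 0 | 1.00 | 81% | 1.00 | 81% |
| 0.005 | 1.295 | 70% | 1.235 | 72% |
| 0.01 | 1.59 | 61.5% | 1.47 | 65% |
| 0.02 | 2.18 | 49% | 1.94 | 53% |

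Worked line, ICC 0.01 and m = 48: 67.2 / 1.47 = 45.7 effective events; 0.693 × √(45.7/4) = 2.34; 2.34 − 1.96 = 0.38; power 65%. A t reference with 18 degrees of freedom (20 camps less 2) lowers the 0.01 row to about 57% and 60%.

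**3. Children needed for 80% with 10 camps per arm.** If n₀ is the unclustered number per arm, then n = 10 × n₀ × (1 − ICC) / (10 − n₀ × ICC).
- *Retained basis*, n₀ = 933.5/2 = 466.75. ICC 0.01: 10 × 466.75 × 0.99 / (10 − 4.67) = 866.5 retained; 866.5 / 0.80 = about 1,083 enrolled per arm (108 per camp).
- *Enrolled basis*, n₀ = 1166.9/2 = 583.4. ICC 0.01: 10 × 583.4 × 0.99 / (10 − 5.83) = about 1,390 per arm (139 per camp).
- ICC 0.02, retained basis: 10 × 466.75 × 0.98 / (10 − 9.335) = about 6,880 retained, or about 8,600 enrolled per arm.

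**4. What a larger exhaustive sample would buy at ICC 0.01.**

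| Enrolled per camp | Power, enrolled m | Power, retained m |
|---|---|---|
| 60 | 61% | 65% |
| 100 | 74% | 78% |
| 150 | 81% | 86% |

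**The case against.** **The protocol expects more than 1,200 children.** This is the strongest reply. At ICC 0.01, about 108 enrolled children per camp (retained basis) would bring power back to 80%, and the surveillance may well reach that. So it is not shown that the trial is underpowered. But the article gives no expected count and does not offer the larger sample as an allowance for clustering. The reply leaves actual power unknown and does not rescue 80% at 600 per arm.

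**The 0.01 belongs to another outcome.** This stands. It was stated for a mean diet score in a survey, and incidence could cluster less or more. At ICC 0.001, power at 600 per arm would be about 79%. Any single power figure is therefore conditional; the absence of a clustering allowance is not.

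**The arithmetic is correct.** It is, for the inputs listed. The fault is a missing design input.

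Three stronger readings are tempting and are not supported:
- *Power is 61%.* That counts lost children in the cluster size after removing them from the events. Counting retained children in both gives 65%, so 61% is the lower end of a range.
- *At ICC 0.02, 80% cannot be reached however many children are measured.* That follows only on the enrolled basis, where the denominator is negative (10 − 11.67). On the retained basis it is positive, and the requirement is about 8,600 per arm: impractical, but finite.
- *The 7% is really the untreated risk, so events are overstated further.* The article assumes "the proportion of the population under surveillance that would develop GAM during 6 months was 7" per cent, and the surveillance covers both arms. Read literally, that is the overall risk, which is how the calculation uses it. The guidance behind it is not shown, so nothing supports the other reading.

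**Conclusion.** The concern holds. The 1167 (600 per arm) is the size for individually allocated children, and the 80% attached to it is not the power of a design with 10 camps per arm. That part rests only on the article's own figures.

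The size of the shortfall rests on an assumed ICC and on the usual design-effect approximation applied to events. At 600 per arm, power is about 61% to 65% at ICC 0.01, about 70% or slightly more at 0.005, and about 50% at 0.02. At ICC 0.01 the exhaustive sample makes good the loss only from about 1,083 to 1,390 children per arm; at 0.02 this is practically out of reach with the camps available. Since the article gives neither an ICC for incidence nor camp sizes, the power actually available is undetermined.

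**What to change.** Replace the 1167/600 statement with a clustered calculation that gives:

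1. an ICC assumed for incidence, labelled as an assumption, with a sensitivity range (for example 0.005, 0.01 and 0.02);
2. 10 camps per arm;
3. the expected number of children per camp from the exhaustive listing;
4. one consistent cluster size, so that children lost to follow-up are treated alike in the event count and the design effect.

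Report the resulting power range in place of 80%. At ICC 0.01 this would read, for example, 61% to 65% with 60 enrolled children per camp, 74% to 78% with 100, and 81% to 86% with 150; the upper figure in each pair is on the retained basis.

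The cost is a recalculation and a revised paragraph. No extra children or camps are needed, because every eligible child in the study camps is already to be measured. The price is a stated power that may be less favourable.

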### Data collection

Quantitative data will be collected using questionnaires translated into the local Somali language, and addressed to the primary carer of the child included in the study. A two-week training will be implemented for enumerators and supervisors prior to survey implementation. During this training we will pilot questionnaires. Survey data will be collected using mobile devices and community surveillance data will be collected on paper.

The study and data collection timelines are outlined in Table 1. Baseline and endline surveys will take place in March and June 2016, respectively. The community surveillance system will start data collection in March 2016 and will continue for about 1 year.

**Table 1 Tab1:** REFANI-S intervention and data collection timeline

Study component	Month						
	Feb	Mar	Apr	May	Jun	Jul	Aug
Intervention		x	x	x	x	x	
Community surveillance system	x	x	x	x	x	x	x
Malnutrition risk factor surveys	x				x		

Four teams, each with two enumerators and led by two supervisors, will undertake data collection for the surveys. The qualitative data collection will be undertaken by one team with a supervisor. For the surveillance system, a total of 16 CHW will collect data, grouped into 4 teams of 4 members, each team with one supervisor. A field coordinator and a study coordinator will supervise all field-teams. All the study team except the study coordinator will be local staff and will be based in the Mogadishu area. Qualitative data will be collected by a trained team in the local Somali language.

### Outcome measures

The primary outcome measures are (1) incidence of acute malnutrition in children aged 6–59 months, as defined as a MUAC <12.5 cm and/or the presence of bilateral pitting oedema; and (2) mean individual diet diversity scores values of children aged 6–59 months.

The secondary outcome measures are (1) prevalence of GAM, as defined as a weight-for-length/height z-score < −2 (WHO 2006 Growth Standards) and/or bilateral pitting oedema in children aged 6–59 months; (2) mean weight-for-length/height values in children aged 6–59 months; (3) mean 30-day household expenditure; (4) mean household dietary diversity score, obtained using 24-h recall data; (5) mean household food insecurity access scale score, obtained using one-month recall data; (6) mean coping strategies index values, obtained using a 7-day recall data; (7) mean maternal MUAC; (8) mean maternal BMI.

